**Glossary**

DRC Democratic Republic of Congo

MIP Médecin Inspecteur Provincial

MSF-OCA Médecins Sans Frontières – Operational Centre Amsterdam

Plumpynut® A type of Ready To Use Therapeutic Food

RDI Recommended Daily Intake

RUTF Ready to Use Therapeutic Food

TFP Therapeutic Feeding Program

WHO World Health Organisation

**A randomised intervention study to evaluate the effectiveness of RUTF for catch up growth in children younger than 5 five years after an episode of malaria caused by *Plasmodium falciparum* in Dubie, Katanga, DRC.**

**Study Location:**

Dubie, Katanga, South DRC

**Objective:**

The primary objective of this study is to determine to what extent provision with RUTF will promote catch up growth in children following an acute uncomplicated episode of *P.* *falciparum* malaria.

**Method:**

Randomised intervention study.

**Number of patients:**

100 patients provided with 92 g (500 kcal) Plumpynut® (aReady To Use Therapeutic Food (RUTF)) for 14 days, and 100 patients not provided with RUTF.

**Inclusion:**

Children aged 6 – 59 months with *P. falciparum* malaria, confirmed by thick film microscopy

**Exclusion:**

- - Children who are exclusively breast fed
  - Children who are severely malnourished
  - Presence of severe malaria

**Main outcome:** Average weight gain at 2 weeks post-enrolment in the group supplemented with RUTF, compared to the group not supplemented.

**Secondary outcomes:**

- Proportion of children not gaining weight in both groups
- Average weight gain at two weeks from the last day of supplementation.
- Contribution of other factors (potential confounders such as duration of malaria before treatment) to convalescence after an episode of malaria.

**A randomised intervention study to evaluate the effectiveness of RUTF for catch up growth in children younger than 5 five years after an episode of *P.falciparum* malaria in Dubie, Katanga, DRC.**

# 1. INTRODUCTION

**1.1 The inter-relationship between infection and malnutrition**

The aetiology of malnutrition in most tropical countries is multi-factorial, not only involving an inadequate diet but also recurrent infections.[[1]](#endnote-2) Specifically young children have a high exposure to acute infectious diseases (diarrhoea, acute respiratory infection) and they are at high risk of developing malnutrition. In many countries the situation seems to have worsened in recent years.[[2]](#endnote-3)

Infections are generally associated with weight loss during the illness. This occurs because infections may 1) decrease food intake (anorexia); 2) impair nutrient absorption; 3) cause direct nutrient losses; 4) increase metabolic requirements or catabolic losses; and 5) impair transport of nutrients to target tissues. Fever can account for 20-30% of reduced intake.[[3]](#endnote-4) In addition infections can cause increased losses (malabsorption, diarrhoea) and increased utilisation of nutrients (increased secretion in the gut, internal diversion for metabolic responses, increased metabolic rate when fever is present).[[4]](#endnote-5) As increased needs are not compensated by increased consumption, weight loss during an infection is frequent.[[5]](#endnote-6)

The weight loss occurring during an infection is not equal for all infections. Diarrhoea is known to induce weight loss and studies show that also malaria can result in a large weight loss. [[6]](#endnote-7), [[7]](#endnote-8) Lack of convalescence (i.e. failure to return to normal nutritional status) after an infectious disease makes a child more susceptible to further infections such as diarrhoea and malaria that, in turn, will reduce the nutritional state further. 6,7,[[8]](#endnote-9), [[9]](#endnote-10)

Effects of short-term weight loss during episodes of acute infection can be mitigated by good nutrition allowing for catch up growth.[[10]](#endnote-11),[[11]](#endnote-12) However, recovery of nutritional status is often not complete as good nutrition may be lacking. As a consequence a permanently lower nutritional status is established.[[12]](#endnote-13)

**1.2 Prevention of malnutrition**

Catch up growth after an infection is essential for an individual to maintain good nutritional status. In order to prevent malnutrition after an infection the World Health Organisation (WHO) recommends that children are given an extra healthy meal daily, during the two weeks after the onset of the illness.[[13]](#endnote-14) Studies on the effectiveness or impact of this strategy have never been published. However, in many poor regions this strategy is unlikely to be effective, as ingredients of a good meal are not always available and mothers/caregivers often lack resources and time to implement the advice. Therefore a more effective strategy in poor areas may be to provide a child with an infection a high quality supplement, rich in macro- and micronutrients, on contact with the health service. However, there is little evidence to support the effectiveness of this approach, apart from a study done in Gambia.10 In this study it was found that weight loss after acute diarrhoea was corrected by providing a supplement enriched with vitamins and minerals for 2 weeks after an episode of diarrhoea, while during non-intervention periods no significant weight gain occurred. This raises the question to what extent supplementation would be effective for infections other than diarrhoea, such as malaria.

**1.3 Relevance of the study**

Worldwide, malaria kills over a million people and each year 3.2 billion people are at risk. 80% of malaria deaths occur in Africa, where around 66% of the population is at risk.[[14]](#endnote-15) Country wide in the Democratic Republic of Congo (DRC), malaria is responsible for 68% of outpatient visits and 30% of hospital admissions, and accounted for 25-30 % of child mortality in DRC in 2005. Katanga Province had 640 000 reported cases of malaria in 2005 according to WHO statistics.[[15]](#endnote-16) In 2007 the clinics in Katanga supported by MSF-OCA in Katanga saw 54,671 children under five years, of whom 21,939 (40%) were treated for malaria.[[16]](#endnote-17)

The burden of malaria associated with malnutrition is illustrated by the admission profile in the Therapeutic Feeding Centre (TFC) in Dubie, where on average, 44% of the children admitted had/have a positive Paracheck® (February 2007).

Malaria is thus a huge burden on children in Katanga, which additionally puts them at risk of weight loss and poor convalescence 6, 7,[[17]](#endnote-18)

Given the significance of malaria in this setting, this study aims to explore the effectiveness of nutritional supplementation after an episode of malaria in preventing malnutrition. Other studies are also needed to explore the effect of supplementation after episodes of other serious diseases, such as pneumonia and severe diarrhoea.

If shown to be effective, MSF will consider incorporating routine nutritional support in its protocols as supportive therapy of serious infections, such as diarrhoea, malaria and pneumonia as a part of a strategy to prevent of malnutrition.

# 2. HYPOTHESIS

The primary objective of this study is to determine to what extent short-term provision with RUTF (Plumpynut®) will promote growth in children who have been diagnosed and treated for uncomplicated *P. falciparum* malaria. Therefore the following hypothesis will be tested:

Children aged 6-59 months presenting with malaria caused by *P. falciparum* who are provided with a RUTF supplement (Plumpynut®) of 500 kcal/day for 2 weeks will show significantly better catch up growth compared to a similar patient group not provided with RUTF (at 2 weeks and 4 weeks post-intervention).

Specific objectives of this study are:

- To assess the extent of lack of growth associated with an uncomplicated *P. falciparum* malaria episode in children 6-59 months who are not nutritionally supported
- To assess the extent the provision of RUTF for 2 weeks promotes weight gain during and after an uncomplicated *P. falciparum* malaria episode in children 6-59 months, at the end of the 2 weeks of supplementation.
- To assess the extent the provision of RUTF for 2 weeks promotes a sustained weight gain (as measured from presentation with *P. falciparum* malaria to 4 weeks after presentation).
- To assess to what extent other factors contribute to weight change after an episode of non-complicated acute *P. falciparum* malaria.

# 3. STUDY DESIGN AND METHODS

**3.1 Study design**

The study design is that of a randomised intervention study. Children with confirmed *P. falciparum* malaria, meeting all study inclusion criteria, will be enrolled in the study for a period of 28 days. Participants will be assigned at random to either the intervention or the control group.

The intervention group will receive treatment for malaria plus 1 bag of RUTF per day for 14 days. The control group will receive treatment for malaria without provision of RUTF.

Random allocation to either intervention or control group is thought to be acceptable by the population as RUTF is seen as a medicine rather than a food item. A similar study did not meet a problem with randomisation.[[18]](#footnote-2) For other illnesses, the participants will be offered medical treatment according to the best local standards.

Follow-up visits will be scheduled for directly observed treatment for malaria (day 0, 1 and 2), malaria parasite density and clearance (D0, D2, and until slide is negative; and for weight measurements at day 0, 1, 13 and 27. Weight will be measured twice at each visit by two independent observers. A detailed questionnaire will be conducted at the start, and at day 13 and 27.

All participants who attend follow up sessions at the clinic will receive a small incentive[[19]](#footnote-3)* in order to compensate for lost time due to participation in the study (RUTF will not be given to the control group at the end of the study).

The study will be conducted in the period (May-June) that is likely to have a stable prevalence of malnutrition, a stable incidence of *P. falciparum* malaria and other morbidities (e.g. pneumonia and diarrhoea). The total duration of the data collection will be 2 months for data gathering: 4 weeks of enrolment (40 participants per week) and 4 weeks of follow up (the last follow-up being done 4 weeks after the last enrolment).

**3.2. Study population**

The population of study will consist of children aged 6 to 59 months diagnosed with uncomplicated *P. falciparum* malaria consulting the MSF-supported clinics in Dubie, Katanga, South DRC, and whose parent or guardian gives informed consent for study inclusion (see Annex 1).

The children will be selected from villages in close proximity to the clinics (not further than 30 minutes walking distance (approximately 5 kilometres), to minimise loss to follow-up.

**3.2.1 Inclusion criteria**

- Age 6 to 59 months, and
- Positive rapid diagnostic test (Paracheck®) and
- Thick smear showing infection with *P.* *falciparum* and
- Informed consent from parents or guardian aged at least 18 years.

**3.2.2 Exclusion criteria**

- Children who are exclusively breast fed or
- Children who are severely malnourished (MUAC <110 mm and/or bilateral oedema, or WHO weight-for-Height criteria <3 Z-scores) or
- Presence of general danger signs or signs of severe malaria as defined by the WHO criteria, or
- Known history of allergy to malaria drugs, or
- Having a sibling enrolled in the study.

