### Quantity

The 1996 supplementation studyprovided a fortified food ad libitum. The average consumption was 117 kcal/kg/day, and the average study subject weight was between 6.8 and 7.7 kg; this means a total supplement of 796 to 900 kcal/day was given. 10

MSF has chosen to provide a fixed quantity supplement, as currently packaged and used in existing programmes. This contains 500 kcal/day. Although this supplement has a lower energy value than the study in Gambia, it is liked by children and of very high quality. In addition, the energy (calories) provided is not the only criteria for supplementation, as lack of catch up growth also depends on the availability of micronutrients. The supplement must provide at least 1 RDI (Recommended Daily Intake) of the anti oxidant vitamins and minerals important for the production of erythrocytes (Vitamin A, B, C, selenium, zinc, folic acid, copper, iron). One package of Plumpynut® provides about 1 RDI (see annex 6).

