## Follow up of children with a disease who are excluded from the study

- Illnesses in children with or without malaria presenting to the clinic will be treated according to the best standards available to MSF in that community.
- Children with severe malnutrition will be referred to the existing MSF Therapeutic Feeding Program (TFP) to be treated adequately. The 2005 WHO growth standards will be applied, ensuring that all children at risk for mortality related to malnutrition will be selected for therapeutic feeding.

**Independent review:** The Ethical Review Board of MSF will review the study protocol. Up to now there has been no appropriate ethical review committee identified in Katanga. Permission from local authorities in the districts of study will be obtained.

| Annex 2: RUTF malaria recovery study | | | | | | | | | | | | |
| --- | --- | --- | --- | --- | --- | --- | --- | --- | --- | --- | --- | --- |
| Checklist for inclusion/exclusion | | | | | | | | | | | | |
|  | | | |  | |  | | |  |  | |  |
| Paracheck number | | | |  | |  | | |  |  | |  |
| Paracheck positive: | | | | Yes |  | ** Continue** | | |  |  | |  |
|  | | | | No |  | ** Do not enrol in the study** | | | | | | |
|  | | | |  | |  | | |  |  | |  |
| Child between 6 months and 5 years old? | | | | Yes |  | ** Continue** | | |  |  | |  |
|  | | | | No |  | ** Do not enrol in the study** | | | | | |  |
|  | | | |  | |  | | |  |  | |  |
| Date (dd/mm/yy): | | | |  | |  | | |  |  | |  |
|  |  | | |  | |  | | |  |  | |  |
| **A. Danger signs / severe malaria:** | | | | | | | | |  |  | |  |
|  | 1. Unable to drink/breastfeed | | | | | | | |  | Y | | N |
|  | 2. Vomiting everything | | | | |  | | |  | Y | | N |
|  | 3. Recent history of convulsions | | | | | | | |  | Y | | N |
|  | 4. Unable to sit or stand | | | | |  | | |  | Y | | N |
|  | 5. Any other signs of severe malaria (if yes, specify) | | | | | | | | | Y | | N |
|  |  | | |  | |  | | |  |  | |  |
|  | **Any of the questions above answered with Yes?  Do not enrol in the study and refer for immediate treatment** | | | | | | | | | | | |
|  |  | | |  | |  | | |  |  | |  |
| **B. Signs of anaemia** | | | | | | | | |  |  | |  |
|  | 1. Some or severe palmar pallor | | | | | |  | |  | Y | | N |
|  | 2. Mucous membrane pallor | | | | |  | | |  | Y | | N |
|  | 3. Respiratory distress | | | | |  | | |  | Y | | N |
|  |  | | | | | | | | |  | |  |

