| (persistent vomiting several times) | | | | | |  | No |  | |  | | |
|  | |  | |  | |  | Don’t know |  | |  | | |
|  | |  | |  | |  |  |  | |  | | |
| 8. Has your child visited a health facility since your previous visit? | | | | | | | Yes | |  | | |  |
|  | | | | | | | No | |  | | |  |
| 9. Which medication has your child taken since your previous visit? | | | | | | |  | |  | | |  |
| (other than the anti-malaria) | | | | | | | None | |  | | |  |
|  | | | | | | | Drug: | | | | |  |
|  | | | | | | |  | | | | |  |
| 10. Do you feel the child is completely recovered from the malaria episode? | | | | | | | Yes | | | | |  |
|  | | | | | | | No | | | | |  |
| If not, why do you think the child did not recover yet? | | | | | | | Don’t know | | | | |  |
|  | | | | | | |  | | | | |  |
|  | | | | | | |  | | | | |  |
|  | | | | | | |  | | | | |  |
| 11. **During the last 2 weeks** did she/he eat (food or breast milk)? | | | | | | | Much less | | | | |  |
| less then usual, about the same amount, or more than usual. | | | | | | | Somewhat less | | | | |  |
| *IF LESS, PROBE: Was he/she eating much less than usual or somewhat less* | | | | | | | About the same | | | | |  |
|  | | | | | | | More | | | | |  |
|  | | | | | | | Somewhat more | | | | |  |
|  | | | | | | | Much more | | | | |  |
|  | | | | | | | Don’t know | | | | |  |
|  | | | | | | |  | | | | |  |
|  | | | | | | |  | | | | |  |
|  | | | | | | |  | | | | |  |
|  | | | | | | |  | | | | |  |
| **ATTENTION: Question 12, 13 and 14 are only for the RUTF group on day 13** | | | | | | |  | | | | |  |
|  | | | | | | |  | | | | |  |
| 12. During the last 2 weeks how many days did your child eat 1 complete | | | | | | | ........ days | | | |  | |
| Plumpynut? | | | | | | |  | | | | |  |
|  | | | | | | |  | | | | |  |
| 13. How many plumpynut has your child eaten the last 14 days? | | | | | | |  | | | | |  |
|  | | | | | | |  | | | | |  |
| 14 How many empty sachets are returned? | | | | | | |  | | | | |  |
|  | | | | | | |  | | | | |  |

Thank you.

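### Children currently receiving programme RUTF are not excluded, and only the RUTF arm is asked about RUTF intake, so RUTF use by controls cannot be reliably identified

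*Protocol*

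**What the plan says.** - **Control condition (Protocol 3.1).** "The control group will receive treatment for malaria without provision of RUTF".
- **Nutritional exclusion (3.2.2; Annex 2, section C).** "Children who are severely malnourished (MUAC <110 mm and/or bilateral oedema", or weight-for-height below the WHO cut-off. These are measurements on the day of screening. Neither 3.2.1, 3.2.2 nor the rest of the Annex 2 checklist mentions current or recent RUTF, or enrolment in a feeding programme.
- **RUTF outside the trial.** On children with severe malnutrition, section 11 says: "Children with severe malnutrition will be referred to the existing MSF Therapeutic Feeding Program (TFP) to be treated adequately". Section 1.3 places a therapeutic feeding centre in Dubie, the trial site. Section 3.4 says of the supplement: "MSF has chosen to provide a fixed quantity supplement, as currently packaged and used in existing programmes".
- **RUTF intake (Annex 4).** "ATTENTION: Question 12, 13 and 14 are only for the RUTF group on day 13". Question 12 asks on how many days a complete sachet was eaten, question 13 how many were eaten, and question 14 how many empty sachets came back. Annex 3, the enrolment form, has no RUTF item.
- **Items put to every child.** Annex 3 Q28 asks about food aid in the past month. Annex 4 Q8 and Q9 ask about health-facility visits and medicines taken.
- **Adherence (3.2.3).** Eating fewer than 10 sachets is a violation in the treatment arm. There is no counterpart for a control who eats RUTF.

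**The concern.** The contrast of interest is RUTF against none, and the eligibility list and forms do not protect it. A child under rehabilitation who has risen above the severe cut-offs and then gets malaria meets every criterion. If randomised to control, that child may go on eating RUTF, and no form asks about it. The same applies to RUTF that reaches a control from any other source during follow-up.

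Two aims are exposed. The primary objective is to estimate how far RUTF promotes growth, so a diluted difference matters even if the test is still significant. The first specific objective in section 2 describes poor growth in children who get no nutritional support. It rests on the control arm alone, and RUTF use there would make that growth look better than it is.

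A separate analysis plan could not repair this, because the information is not on the data collection forms. RUTF use is also absent from the confounder list in section 5.

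**Working it through.** **1. Which items could reveal RUTF use by a control?**

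| Item | Who and when | Why it falls short |
|---|---|---|
| Annex 2, sections C and D | All, screening | Anthropometry and other criteria; no feeding-programme or RUTF item |
| Annex 3 Q28 | All, enrolment only | General food aid; RUTF not named |
| Annex 4 Q8 | All, both follow-up visits | Yes/no for any facility; no reason recorded |
| Annex 4 Q9 | All, both follow-up visits | Free text on medicines; RUTF not prompted |
| Annex 4 Q12-14 | RUTF arm, first follow-up only | Not asked of controls; not asked of anyone at the second visit |

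Section 3.1 says RUTF is regarded locally as a medicine, not a food. A caregiver might therefore answer no to Q28, yet might mention RUTF under Q9. Detection is possible but not dependable.

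**2. Reproduce the plan's own figure.** Inputs from section 3.3: mean gains over 14 days of 0.09 kg (SD 0.44) in controls and 0.44 kg (SD 0.33) with RUTF; two-sided 5%; 80% power.

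- Difference: 0.44 − 0.09 = 0.35 kg.
- n per group = (1.96 + 0.84)² × (0.44² + 0.33²) / 0.35² = 19.4 (unrounded normal deviates), so 20. This agrees with the plan's 20.

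**3. Worst-case dilution.** Assume that a share f of controls takes RUTF and gains like the intervention arm. The documents give no value for f; the values below are assumptions.

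- Expected difference = 0.35 × (1 − f).
- Control mean = 0.09 + 0.35 × f.
- Power uses 80 evaluable children per group (100 less the plan's 20% loss) and a common SD of √[(0.44² + 0.33²)/2] = 0.389.

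| f | Difference (kg) | Control mean (kg) | Overstatement of control gain | n per group for 80% power | Power, 80 per group |
|---|---|---|---|---|---|
| 0 | 0.350 | 0.090 | none | 20 | 99.99% |
| 5% | 0.333 | 0.1075 | 0.0175/0.09 = 19% | 22 | 99.97% |
| 10% | 0.315 | 0.125 | 0.035/0.09 = 39% | 24 | 99.9% |
| 20% | 0.280 | 0.160 | 0.07/0.09 = 78% | 31 | 99.5% |
| 30% | 0.245 | 0.195 | 0.105/0.09 = 117% | 40 | 97.9% |

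**4. A smaller true effect.** If the true difference were 0.20 kg (an assumption), power with 80 per group would be 90% at f = 0, 83% at 10% and 74% at 20%.

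**The case against.** The case against has several parts, and much of it stands.

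- **The size of the route is unknown.** The documents do not give the programme's caseload or discharge rules, or say whether recovering children take RUTF home. That the product is the one "as currently packaged and used in existing programmes" explains the choice of package; it does not describe distribution in Dubie. This stands, and is why only a range is given.
- **The 44% figure.** A reader might take "44% of the children admitted had/have a positive Paracheck" to show that malaria is common in the children at issue. It describes children on admission to the feeding centre, most of whom the severe-malnutrition criterion would exclude. Section 4.1 adds that the rapid test can stay positive for up to 6 weeks, while entry requires a positive blood film. The figure does not measure malaria in recovering children.
- **Baseline imbalance.** A reader might infer that earlier RUTF makes the arms unequal at entry. Randomisation balances it in expectation, and baseline nutritional status is a listed covariate.
- **No contrast at all.** A reader might assume that affected children contribute nothing. An intervention child who also gets programme RUTF still receives one sachet a day more than a control on programme RUTF. Zero contrast is the extreme case.
- **Closed routes.** A child who becomes severely malnourished is withdrawn (3.2.3), and siblings of enrolled children are excluded, which limits sharing within a household. This narrows the problem but does not remove it.
- **Target population.** Keeping recovered children can be defended in an effectiveness study. That holds for children already discharged, who are no longer on RUTF and keep the full contrast. It does not hold for children still receiving RUTF in a trial whose control condition is none.

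None of this answers the intake gap: the form expressly limits the questions to one arm.

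**Conclusion.** The point holds in a limited form and should be fixed. Eligibility lets in children currently on programme RUTF who are above the severe cut-offs, and the follow-up form confines the intake questions to the RUTF arm. RUTF use by controls could therefore pass unnoticed.

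The expected consequence is an effect estimate diluted towards zero and an overstated control gain. In the worst case the planned difference shrinks by the same proportion as the share of controls affected. That share is assumed, and the worst case supposes that affected controls gain as much as the intervention arm.

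Two stronger conclusions are not supported. The trial is not shown to be underpowered: at 0.35 kg, power stays above 97% even with 30% of controls affected, and becomes a concern only if the true effect is well below plan. Nor is such use wholly invisible, since three indirect items are asked of every child. No figure stated in the plan is wrong on this account.

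**What to change.** 1. **Eligibility.** Add to 3.2.2 and Annex 2 section D: currently enrolled in a feeding programme that provides RUTF. Because 3.2.3 withdraws a child in whom an exclusion criterion develops later, state whether this line applies at screening only.
2. **Enrolment form.** Add to Annex 3 an item on recent RUTF use or recent discharge from a feeding programme. Use it as a baseline covariate, not as an exclusion; excluding discharged children would not address concurrent use.
3. **Follow-up form.** In Annex 4, ask both arms at both visits whether RUTF from any source was eaten and how many sachets. In the RUTF arm, also ask about RUTF from outside the study. Lifting the present restriction alone would not do, because the returned-sachet count (Q14) makes sense only for the RUTF arm and should stay there.
4. **Reporting.** Report RUTF use by arm and examine it in a sensitivity analysis.

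The cost is one checklist line, a short enrolment item, one extra follow-up question and a few more screen failures. If contamination proves rare, the follow-up question is what lets the sponsor show it.

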The sample will be drawn from the group of children who come to the clinic, have been clinically reviewed and are suspected malaria cases. If the malaria rapid diagnostic test is positive, from this group **one in three** child will be selected randomly, and invited to join the study. This selection procedure is necessary as more children will be presenting with malaria then study can process in a day. After explaining the study and the consent procedure, the patient will be randomly allocated to either the control group or the intervention group. The random number function of a pocket calculator will be used for randomisation. In the first step numbers ending on 3,6 and 9 will be invited for the study, numbers ending on 1,2,4,5,7,8, will not be invited, and when a number ends no 0 a new random number will be generated. Numbers ending on an even number or a zero will be in the intervention group, numbers ending on uneven will be in the control group.

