|  | **Any of the questions above yes? Test Hb; HB<5 g/dL?  Do not enrol in the study and offer normal treatment** | | | | | | | | | | |  |
|  |  | | |  | |  | | |  |  | |  |
| **C. Severe malnutrition** | | | | | | | | | | | | |
|  | 1. Bilateral oedema | | | | | | | Yes | | **No** |  | |
|  | 2. MUAC < 11 cm | | | | | | | Yes | | **No** |  | |
|  | 3. Weight-for-Height < -3sd WHO 2005 reference | | | | | | | Yes | | No |  | |
|  |  | | |  | |  | | |  |  | |  |
|  | **Any of the questions above answered with Yes?  Do not enrol in the study and refer for immediate treatment in the TFP** | | | | | | | | | | | |
|  |  | | |  | |  | | |  |  | |  |
| **D. Other criteria - please tick:** | | | | | |  | | |  |  | |  |
|  | 1. Serious concomitant illness | | | | |  | | |  | Y | | N |
|  | 2. History of allergy to anti malarial drugs | | | | | | | |  | Y | | N |
|  | 3. History of allergy to peanuts or milk | | | | | | | | | Y | | N |
|  | 4. Exclusive breastfeeding | | | | | | | | | Y | | N |
|  | 5. Sibling enrolled in this study | | | | | | | | | Y | | N |
|  | 6. Lives further away than 30 min walking distance | | | | | | | |  | Y | | N |
|  | (check name of village) | | | | | | | |  |  | |  |
|  | **Any of the questions above answered with Yes?  Stop** | | | | | | | | | | |  |
|  |  | | |  | |  | | |  |  | |  |
| **E. Consent:** | | | | | | | | |  |  | |  |
| *Explain the study and read out consent form* | | | | | | | | |  |  | |  |
|  | Guardian > 18 and close relative, gives consent | | | | | | | |  | Y | | N |
|  | |  | | | | | | |  |  | |  |
| Included? | Y | | N |  | | | | |  |  | |  |
|  |  | |  |  | | | | |  |  | |  |
| Study ID number |  | |  |  | | | | |  |  | |  |

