| 22. Do you mainly work on your own land or on family land, or do you work | | | | | | | | Own land | | | |  | | |  |
| on land that you rent from someone else, or do you work on someone else’s land? | | | | | | | | Family land | | | |  | | |  |
|  | | | | | | | | Rented land | | | |  | | |  |
|  | | | | | | | | Someone else’s land | | | |  | | |  |
|  | | | | | | | |  | | | |  | | |  |
|  | | | | | | | |  |  | | |  | | |  |
| 23. How many hectares of agricultural land do members of this household own? | | | | | | | | None | | | |  | | |  |
| (in total) | | | | | | | | ............ | | | | Hectares | | |  |
| (Household definition: people sleeping in the same house and eating from the same cooking pot) | | | | | | | | Don’t know | | | |  | | |  |
|  | | | | | | | |  |  | | |  | | |  |
| 24. Does any member of your household own | | | |  | | | | Yes | No | | | Don’t know | | |  |
|  | | | | A watch | | | |  |  | | |  | | |  |
|  | | | | A bicycle | | | |  |  | | |  | | |  |
|  | | | | A radio | | | |  |  | | |  | | |  |
|  | | | | Have a generator for electricity | | | |  |  | | |  | | |  |
|  | | | | | | | |  |  | | |  | | |  |
|  | | | | | | | |  |  | | |  | | |  |
| 25. Does this household own any livestock, herds, other form animals, or poultry? | | | | | | | | Yes | | | |  Q26 | | |  |
|  | | | | | | | | No | | | |  Q27 | | |  |
|  | | | | | | | | Don’t | know | | |  Q27 | | |  |
|  | | | | | | | |  |  | | |  | | |  |
|  | | | | | | | |  |  | | |  | | |  |
| 26. How many of the following animals does this household own? | | | | | | | |  |  | | |  | | |  |
|  | | | |  | | | |  |  | | | Number | | |  |
|  | | | |  | | | | Goats | | | |  | | |  |
|  | | | |  | | | | Sheep | | | |  | | |  |
|  | | | |  | | | | Chicken / other poultry | | | |  | | |  |
|  | | | |  | | | | Pigs | | | |  | | |  |
|  | | | |  | | | | Cows | | | |  | | |  |
|  | | | | | | | |  |  | | |  | | |  |
| 27. What is the main material of the external walls of your house? | | | | | | | |  |  | | |  | | |  |
|  | | | |  | | | | Yes | No | | | Don’t know | | |  |
|  | | | | Improvised: plastic, cloth, timber | | | |  |  | | |  | | |  |
|  | | | | Wood, mud, bamboo | | | |  |  | | |  | | |  |
|  | | | | Stone, brick, cement | | | |  |  | | |  | | |  |
|  | | | | Don’t know | | | |  |  | | |  | | |  |
|  | | | |  | | | |  |  | | |  | | |  |
|  | | | | | | | |  |  | | |  | | |  |
|  | | | | | | | |  |  | | |  | | |  |

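### The co-enrolment bar covers siblings only, so other children of one household can be randomised to opposite arms and supplement eaten by the control child would go unrecorded

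*Protocol*

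**What the plan says.** Section 3.2.2 excludes a child on the ground of "Having a sibling enrolled in the study". The screening checklist in Annex 2 repeats this as item D5, "Sibling enrolled in this study". No other criterion, checklist item or allocation rule mentions the household.

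Section 3.3 allocates each child separately: "the patient will be randomly allocated to either the control group or the intervention group", by the last digit of a random number, in a 1:1 ratio.

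Section 3.1 describes the supplement: "The intervention group will receive treatment for malaria plus 1 bag of RUTF per day for 14 days". Only the malaria treatment is described as directly observed (section 7.4).

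Annex 4 measures intake by caretaker report and a count of returned empty sachets, with the instruction "ATTENTION: Question 12, 13 and 14 are only for the RUTF group on day 13".

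Annex 3, question 23, contains a definition, "Household definition: people sleeping in the same house and eating from the same cooking pot", but uses it only to ask about land ownership.

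**The concern.** A household in the sense of Annex 3 is wider than a set of siblings. Two cousins under five who eat from one pot pass both section 3.2.2 and item D5. If they fall in opposite arms, there is a supply of sachets in the home of a control child.

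That the sachets are eaten at home is an inference, though a firm one. The scheduled visits in section 3.1 are on days 0, 1, 2, 13 and 27, the supplement runs for 14 days, and empty sachets are brought back to be counted.

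What a control child eats raises the control mean and pulls the comparison toward no difference. The planned data could not show this or correct for it: controls are not asked about RUTF, and an empty sachet does not show who ate the contents. The withdrawal rule in section 3.2.3, for fewer than 10 sachets in two weeks, concerns the RUTF child alone. If that child is withdrawn, the supplemented control stays.

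**Working it through.** **The plan's own figure.** Section 3.3 gives means of 0.09 kg (SD 0.44) and 0.44 kg (SD 0.33), hence a difference of 0.35 kg, with a two-sided 5% level and 80% power.

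n = (0.44² + 0.33²)(1.960 + 0.842)² / 0.35² = 19.38, rounded up to 20 per group. This agrees with the stated 20. The plan then proposes 100 per group.

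**Formula for the avoidable loss.** Let f be the share of participants who belong to a non-sibling, same-household, opposite-arm pair, and s the share of the sachets that passes to the control child. With 1:1 allocation, a share f of the control arm gains s × 0.35 kg each. This assumes that the gain is proportional to the sachets eaten and that the two children's 14-day periods coincide. The difference between arms falls by the fraction f × s.

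The RUTF child's own loss is left out. Under a wider rule the cousin still lives in the home and can still eat the sachets; the cousin is merely not enrolled. Only the control-side gain is removed.

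**Inputs.** The protocol gives neither f nor s. Equal sharing, s = 0.5, is assumed, and f is taken by two routes.

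- *Route A (assumption):* 2-8% of participants live with a non-sibling participant, half of them in opposite arms, so f = 0.01-0.04.
- *Route B (section 3.3 figures plus an assumption):* there are 600 cases in four weeks and 1 in 3 is sampled. Assume that 2-20% of the cases belong to non-sibling same-household pairs, that is 6-60 pairs. Both children are sampled with chance 1/9 and fall in opposite arms with chance 1/2, giving 6/18 = 0.33 to 60/18 = 3.33 pairs. Among 200 participants, f = 2 × 0.33/200 = 0.0033 to 2 × 3.33/200 = 0.033.

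**Results.**

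| Route | f | f × s | Remaining difference |
|---|---|---|---|
| A | 0.01-0.04 | 0.5-2.0% | 0.348-0.343 kg |
| B | 0.0033-0.033 | 0.17-1.7% | 0.349-0.344 kg |

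**Power.** At 0.343 kg, the lowest value in the table, the required number is 19.38 × (0.35/0.343)² = 20.2, rounded up to 21 per group. With 80 analysed per group (100 less 20% loss), power is still about 99.99%.

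**The 10-sachet rule.** An equal split of 14 sachets leaves 7, below 10, so a truthfully reported equal split leads to withdrawal of the RUTF child. A child who stays in can have given away at most 4 of 14, or 29%. This limits the RUTF child's loss among those retained. It does not remove the control child's gain.

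**The case against.** The strongest case against is that nothing here is misstated. Section 3.2.2 and Annex 2 agree with each other, the protocol does not say why siblings are excluded, and the household definition belongs to a question on land. That stands: preventing shared food is a plausible purpose of the rule, but it is an inference, and widening the rule is an improvement rather than the repair of a contradiction.

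Sharing itself is a possibility, not something the documents report. Section 3.1 says that RUTF is regarded locally as a medicine rather than a food, which counts against it. Enrolment runs over four weeks, so two children's supplement periods may overlap only in part. Route A is also generous: with 1-in-3 sampling, 2-8% of participants would require about 6-24% of all cases to be in such pairs.

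Four stronger readings are tempting, and the documents do not support them.

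- A reader might count the loss twice, once for the RUTF child and once for the control, and call 1-4% of the difference (0.347-0.336 kg) avoidable. The RUTF child can lose sachets to an unenrolled cousin just as well, so only half of that is avoidable.
- A reader might add half-siblings to those who slip through. The protocol does not define sibling, and ordinary usage includes them.
- A reader might infer that correlation within households invalidates the regression. Few pairs are expected, and in opposite-arm pairs a positive correlation lowers the variance of the contrast. Harm is not shown.
- A reader might take Annex 3's list of grandparents and other relatives as proof of mixed households. It shows who may answer the questionnaire, not how many families' children share a house.

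**Conclusion.** The gap is real and small. Non-sibling children of one household can be randomised to opposite arms, and RUTF eaten by the control child would not be recorded by any planned measurement. The bias runs toward no difference. The avoidable part is about 0.2-2% of 0.35 kg, leaving roughly 0.349-0.343 kg. This rests on assumed rates of shared households, equal sharing, fully coinciding supplement periods and a gain proportional to intake; the protocol gives none of these. Less sharing or less overlap would make it smaller. A reader might infer a threat to the sample size, but 100 per group against a need of 20 leaves ample power. The reason to act is that the bias could not be seen afterwards and costs almost nothing to prevent.

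**What to change.** In section 3.2.2 and in Annex 2 item D5, replace the sibling wording by: a sibling, or another child of the same household, already enrolled in the study. Print the Annex 3 household definition (same house, same cooking pot) beside both, so that screening staff apply it uniformly. The check takes place at screening, before consent and allocation, so it does not affect the comparability of the arms.

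The cost is one phrase in two places and one more question to the caretaker. A few otherwise eligible children would not be enrolled. Section 3.3 reports 600 cases in four weeks against 200 places, so they are easily replaced.
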